# Digital crowdsourced intervention to promote HIV testing among MSM in China: study protocol for a cluster randomized controlled trial

**DOI:** 10.1186/s13063-020-04860-8

**Published:** 2020-11-17

**Keywords:** HIV testing, Men who have sex with men (MSM), Digital, Crowdsourced intervention, Cluster-randomized controlled trial, China

## Abstract

**Background:**

Men who have sex with men (MSM) are an important HIV key population in China. However, HIV testing rates among MSM remain suboptimal. Digital crowdsourced media interventions may be a useful tool to reach this marginalized population. We define digital crowdsourced media as using social media, mobile phone applications, Internet, or other digital approaches to disseminate messages developed from crowdsourcing contests. The proposed cluster randomized controlled trial (RCT) study aims to assess the effectiveness of a digital crowdsourced intervention to increase HIV testing uptake and decrease risky sexual behaviors among Chinese MSM.

**Methods:**

A two-arm, cluster-randomized controlled trial will be implemented in eleven cities (ten clusters) in Shandong Province, China. Targeted study participants will be 250 MSM per arm and 50 participants per cluster. MSM who are 18 years old or above, live in the study city, have not been tested for HIV in the past 3 months, are not living with HIV or have never been tested for HIV, and are willing to provide informed consent will be enrolled. Participants will be recruited through banner advertisements on Blued, the largest gay dating app in China, and in-person at community-based organizations (CBOs). The intervention includes a series of crowdsourced intervention materials (24 images and four short videos about HIV testing and safe sexual behaviors) and HIV self-test services provided by the study team. The intervention was developed through a series of participatory crowdsourcing contests before this study. The self-test kits will be sent to the participants in the intervention group at the 2nd and 3rd follow-ups. Participants will be followed up quarterly during the 12-month period. The primary outcome will be self-reported HIV testing uptake at 12 months. Secondary outcomes will include changes in condomless sex, self-test efficacy, social network engagement, HIV testing social norms, and testing stigma.

**Discussion:**

Innovative approaches to HIV testing among marginalized population are urgently needed. Through this cluster randomized controlled trial, we will evaluate the effectiveness of a digital crowdsourced intervention, improving HIV testing uptake among MSM and providing a resource in related public health fields.

**Trial registration:**

ChiCTR1900024350. Registered on 6 July 2019.

## Background

Chinese MSM still have a high burden of incident HIV infection, suggesting the need for enhanced HIV control strategies. As of October 2019, MSM accounted for 23.0% of newly reported HIV cases in China, increased from 14.7% of new HIV cases in 2011 [1, 2]. Although the Chinese clinical and public health systems have organized many free HIV testing programs, two systematic reviews show that the HIV testing rate among MSM in China remains low [3, 4]. In order to improve the HIV testing rate and reach the first 90 target of the 90-90-90 UNAIDS goals [5], innovative approaches are urgently needed. Digital crowdsourced media may be a useful tool. We define digital as social media, mobile phone applications, Internet, or other approaches that use digital connections.

Digital approaches have been used to promote HIV prevention, especially for key populations like MSM [6–9]. Digital approaches can reach remote participants, limit stigma, provide a platform for anonymity and privacy, and increase community engagement [7, 9–11]. Previous surveys suggested that digital interventions can promote HIV testing and safe sexual behaviors through providing information related to HIV, offering HIV testing services, collecting different creative ideas to design intervention and linking people to the community [10, 12]. In China, the Internet has become a major way to find gay partners among MSM [13, 14]. A cross-sectional survey of 61 cities in China showed that 73.5% of MSM had found recent sex partners online [15], providing a strong foundation for digital interventions. According to the data of MSM national sentinel surveillance in China, only 26.3% men had received an HIV test and know the results in the last year [16]. The high rates of Internet use and low HIV testing rate among MSM in China make digital approaches a useful tool in reaching high-risk populations and building low-cost HIV prevention interventions to promote HIV testing [17, 18].

Crowdsourcing provides an opportunity to develop HIV testing services tailored to meet local community needs while [19, 20]. Crowdsourcing has a group of experts and non-experts working together to solve a common problem and sharing solutions with the public [19, 21]. Crowdsourcing may be useful in health research and has been used in cancer, malaria, and HIV research [22–25]. It has several advantages. First, crowdsourcing provides a platform for the people who have no formal training to make a contribute and enhance community engagement [20, 26–28]. Second, crowdsourcing approaches have been found effective in many trials [24, 29]. Third, crowdsourcing can help to access vulnerable groups that would otherwise be difficult to engage [27, 30]. As a result, crowdsourcing also represents a relatively low-cost method to collect information from a large number of people [20, 24, 28, 31]. However, most crowdsourced interventions have been conducted in large cities with few in smaller cities and less developed areas [29, 32]. Digital crowdsourced media may be a good way to promote HIV testing and healthy sexual behaviors in rural or remote regions.

This study proposal aims to describe the designing of the cluster RCT and to evaluate the efficacy of digital crowdsourced intervention to improve HIV testing uptake among MSM in China.

### Trial aims

The first aim of this trial is to improve HIV testing uptake among MSM in eleven target cities. The study will evaluate the effectiveness of a digital crowdsourced intervention compared to current HIV interventions organized by local centers for disease control and prevention (CDCs). We hypothesize that the digital crowdsourced intervention will be superior in improving HIV testing uptake. The second aim is to compare secondary outcomes (including condom use, social networking, HIV stigma, and others) between the digital crowdsourced intervention arm and the current HIV intervention. We hypothesize that the digital crowdsourced intervention will be superior in promoting safe sexual behaviors.

## Methods

### Design

As the intervention in our study will involve two levels—the community level and the individual level, and MSM in the same city often communicate with each other, we adopt a cluster-randomized controlled trial with one intervention arm and one control arm (Fig. 1). The cluster unit will be the city. Surveys will be conducted at baseline and every 3 months thereafter (Fig. 2). A total of ten clusters, including City A, City B, City C, City D, City E, City F, City G, City H, City I, City J, and City K from Shandong Province, were chosen based on the following criteria: (1) CDC MSM sentinel surveillance sites and (2) capacity for recruiting sufficient MSM. City J and a nearby City K are in the same cluster because the number of estimated MSM in both cities is small.

**Fig. 1 Fig1:**
[figure not shown]
Schematic of crowdsourced intervention implementation

**Fig. 2 Fig2:**
[figure not shown]
SPIRIT figure of study timeline

### Participants and eligibility criteria

Eligibility criteria for participants were as follows: (1) aged at least 18 years, (2) had anal sex with men in the past 1 year, (3) currently living and planning to live in the city for the next 12 months, (4) born biologically male, (5) agree to provide phone number (just for follow up), (6) willing to participate in the follow-up survey every 3 months, and (7) fully understand the facts about the trial with the informed consent. The informed consent form will be shown to the potential participants at the beginning of the online questionnaire. Only those who clicked the “agree” option may be included in the study. Participants living with HIV will be invited to complete the baseline survey but will not be followed.

### Study measures and recruitment

We have built an online questionnaire (see Additional file 1) using Sojump Survey Software. The questionnaire is divided into two parts. Part 1 includes the informed consent form and six items related to study eligibility. Part 2 includes the main items related to this trial. MSM who are determined eligible in the first part proceed to the second section. They will be required to add us as contacts on WeChat (the largest social mobile phone app in China) so that we can establish an online cohort. Participants who do not meet all requirements can scan the QR codes to get 0.14USD (1RMB) on WeChat as an inducement. MSM will be recruited through banner advertisements on Blued, the largest gay dating app in China. CBOs in each study city will also assist with recruitment. In addition to direct recruitment through digital approaches, eligible participants will be invited to refer no more than five friends from their social networks of MSM and can receive a 1.44USD (10RMB) per person as incentive if their friends meet the requirements of this trial. All participants who enroll in the trial will receive a 7.22USD (50RMB) incentive for baseline survey and 7.22USD (50RMB) for each follow-up. Surveys will be conducted at baseline and every 3 months thereafter. Those who complete all five surveys will have an opportunity to win an iPad mini.

All the information in the questionnaire is self-reported. The questionnaire used in MSM surveillance sites run by local CDCs in each city will include additional questions about sexual partners, social media engagement, HIV/syphilis testing, and HIV/syphilis test results (see Additional file 2). Cell phone numbers will be used to link CDC and online survey data sets so the self-report data can be triangulated with CDC surveillance data during the same period.

### Follow-up

All participants will receive an online survey at baseline and follow-up surveys will be conducted every 3 months. Each man will participate in a total of five surveys. At the 2nd and 3rd follow-ups, we will send self-test kits to the participants in the intervention group to evaluate the effectiveness of self-test kit in improving HIV testing rate.

### Outcomes

The primary outcome of this study will be the uptake of self-reported HIV testing uptake after 12 months. We have set ten monitoring sentinels in the eleven cities so that the self-reported HIV testing rate can be triangulated with the rate from surveillance data during the same period. In addition, participants who receive the self-test kit are required to send their results to us on WeChat so that we can verify that the self-reported results are consistent with the self-test results. An increase of 20% in testing rate (assuming a proportion of HIV testing of 70% in intervention arm and 50% in control arm) was chosen as the superiority margin. This choice was based on the data of MSM sentinel surveillance collected by CDCs of Shandong Province in last 1 year. Secondary outcomes include condom use, syphilis testing, social network characteristics, and others (see Additional file 4).

### Sample size

A two-arm, cluster-randomized controlled trial will be used. The sample size was calculated based on the primary outcome. We assumed that a digital crowdsourced intervention will be superior to CDC routine intervention in promoting HIV testing rate among MSM who have not been tested in the past 3 months. Assuming the HIV testing rate is 70% in intervention cities and 50% in the control cities, a total of ten clusters (five in intervention group and five in control group), an intraclass correlation coefficient of 0.02 (usually between 0.01 to 0.03), two-sided *α* = 0.05, power = 0.85, and the loss of follow-up is 30%, the total sample size is 500 men (50 for each cluster). The calculation was made using the software PASS 15.

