### Analysis

The socio-demographic characteristics will be analyzed using descriptive statistics. Comparison in baseline characteristics between the intervention and control arm will be conducted using a chi-squared test adjusted for clustering. The primary outcome of this trial will be the uptake of self-reported HIV testing rate after 12 months. Generalized linear mixed models (GLMM) will be used for the analysis. Intervention status and time will be considered fixed effects, while sites and individual participants with multiple measurements across the four follow-ups will be considered random effects.

The secondary outcomes will include a series of binary variables (continuous variables will be categorized into binary variables), such as number of sexual partners, frequency of anal sex, sex without condoms, frequency of HIV testing (including both facility-based and self-testing), awareness of syphilis status, social network engagement, and others. These will be analyzed similar with the primary outcomes. Furthermore, the interaction effect of intervention between individual level and community level will also be analyzed.

After the 2nd follow-up, we will conduct an interim analysis to evaluate the effectiveness of digital images and videos. After the 4th follow-up, we will also evaluate the effectiveness of digital media and self-test kit using data collected from the 3rd and 4th follow-ups.

The data cleaning, sorting, and analysis will be carried out by team members who do not participate in the randomization and city administration and do not know the treatment allocation. Data analysts were not allowed to modify or delete data. If an outcome is missing for < 15% of participants, analyses will use a complete-case approach. Otherwise, multiple imputation will be used. Participants who miss the follow-up will be included and assumed not achieve the primary and secondary outcomes during the missed follow-up period.

We will also carry out a subgroup analysis based on age (> 30 years old versus ≤ 30 years old) and way of HIV testing (facility-based versus self-testing).

In order to measure contamination, we will conduct per protocol sub analyses to measure whether our results have been affected by contamination.

Results of this study will be distributed to target cities and national stakeholders.

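### The 85% power for 500 men rests on a normal-theory test; with the 8 between-city degrees of freedom that ten clusters provide, power under the protocol's own assumptions is about 75%

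*Protocol article*

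**What the plan says.** The Sample size section of the protocol article gives every input:

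- Rates: "Assuming the HIV testing rate is 70% in intervention cities and 50% in the control cities".
- Clusters: "a total of ten clusters (five in intervention group and five in control group".
- Correlation: "an intraclass correlation coefficient of 0.02 (usually between 0.01 to 0.03".
- Error rates: "two-sided *α* = 0.05, power = 0.85".
- Loss and result: "power = 0.85, and the loss of follow-up is 30%, the total sample size is 500 men (50 for each cluster".

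It names the software (PASS 15) but not the test behind the figure. Trial status adds that the sample size was recalculated when the design became ten clusters.

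For the primary outcome, the Analysis section says "Generalized linear mixed models (GLMM) will be used for the analysis", with intervention and time as fixed effects and site and participant as random effects. It gives no degrees of freedom or reference distribution.

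The Outcomes section describes the 20-point increase thus: "assuming a proportion of HIV testing of 70% in intervention arm and 50% in control arm) was chosen as the superiority margin". Trial aims states an ordinary superiority hypothesis with no margin.

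**The concern.** Cities are randomized, so the intervention effect has to be judged against variation between cities within arms. Ten cities in two arms leave 10 − 2 = 8 degrees of freedom for that variation, and the 5% two-sided critical value is then 2.306 rather than 1.96. A power figure based on 1.96 treats the between-city variance as known.

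If the final test respects the 8 degrees of freedom, the chance of missing the effect the trial was sized for is about one in four, not about one in seven. If it does not, the nominal 5% error rate is exceeded. At the stated ICC and loss, 5% error and 85% power are not obtained together.

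The margin wording is a smaller, separate matter. A superiority margin is the null value that a result must exceed, and the protocol uses the term for the effect it assumes.

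**Working it through.** **Inputs** (all from the Sample size section): p1 = 0.70, p2 = 0.50, five clusters per arm, ICC 0.02 (range 0.01 to 0.03), two-sided 0.05, power 0.85, 30% loss, 50 recruited per cluster. Analysed per cluster: m = 50 × 0.70 = 35, so 5 × 35 = 175 per arm.

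**1. The stated figure.**

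- Design effect: 1 + (35 − 1) × 0.02 = 1.68.
- Variance sum: 0.70 × 0.30 + 0.50 × 0.50 = 0.46.
- Standard error: √(0.46 × 1.68 / 175) = 0.0665.
- Standardised effect: 0.20 / 0.0665 = 3.01.
- Normal-theory power: Φ(3.01 − 1.96) = 0.853. A pooled variance gives 0.838.

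Solving for the size instead: the independent n per arm is 0.46 × (1.960 + 1.036)² / 0.20² = 103.25. Setting 5m / (1 + (m − 1) × 0.02) = 103.25 gives m = 34.5, and 34.5 / 0.7 = 49.25. That rounds up to 50 per cluster and 500 in total, as stated. With the same treatment of loss, the pooled-variance formula gives 530 and the continuity-corrected one 610. All of these take a null difference of zero.

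**2. The same inputs with 8 degrees of freedom.** Power is the probability that a noncentral t on 8 df, with noncentrality 0.20 / SE, exceeds 2.306.

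| Analysed per cluster | ICC | Design effect | Normal-theory power | Power, t on 8 df |
|---|---|---|---|---|
| 35 | 0.01 | 1.34 | 0.921 | 0.838 |
| 35 | 0.02 | 1.68 | 0.853 | 0.751 |
| 35 | 0.03 | 2.02 | 0.784 | 0.673 |
| 50 (no loss) | 0.01 | 1.49 | 0.969 | 0.915 |
| 50 (no loss) | 0.02 | 1.98 | 0.912 | 0.826 |

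At ICC 0.02 the pooled variance gives 0.733 on 8 df. A beta-binomial simulation of a cluster-level t-test (200,000 runs) gave power 0.743 and type I error 5.1%.

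Reaching 85% on 8 df at ICC 0.02 would take 58 analysed per cluster: 58 / 0.7 = 82.9, so 83 recruited per cluster and 830 in all. An 8-df calculation therefore cannot be the source of 500.

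**3. If 1.96 were used with an estimated between-city variance.** P(|t on 8 df| > 1.96) = 0.086. The cluster-level simulation gave type I error 8.6% and power 83.4%. A simulated random-intercept logistic model with a Wald z test rejected in 9.5% of 2,000 null runs; with the 8-df critical value it rejected in 5.3%.

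**4. Sensitivity to the analysis chosen.** The simulated logistic mixed model with an 8-df critical value had power 0.79 at one time point. An analysis that treats the five randomization blocks as pairs has 4 df, with power about 0.62 if pairing removes no variance.

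**The case against.** Five objections deserve an answer.

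- *The calculation accounts for clustering.* It does: ten clusters enter through the design effect, and a reader who infers that they were ignored would be wrong. The omission is limited to the uncertainty of the between-city variance.
- *Degrees of freedom are commonly settled in the analysis plan, which is not shown.* This stands as far as the Analysis section is concerned. Its silence is not an error, and nothing in it commits the trial to a Wald z test. A reader might infer that the planned analysis has a 9% error rate; the protocol does not support that, and the figure applies only if 1.96 is used. The power figure is different, because the protocol states it as a number.
- *The stated error rate and power might still be attained.* In favourable cases, yes: ICC 0.01 with no loss gives 0.915. With the stated 30% loss, power stays below 0.85 across the whole quoted ICC range.
- *0.75 is itself only one figure.* Correct. It is an unmatched, single-time-point, cluster-level value. Repeated measures may add some precision within men but no between-city degrees of freedom. The Analysis section also says that men who miss a follow-up are counted as not achieving the outcome. Taken literally (0.7 × 70% = 49% against 0.7 × 50% = 35%, 50 per cluster), power would be about 0.52 on 8 df and 0.62 by z. The assumptions must therefore accompany the number.
- *The superiority margin makes success almost impossible.* A reader might infer this, since testing against a 20-point null when the true difference is 20 points succeeds only 2.5% of the time. The protocol does not support that reading. Trial aims states plain superiority, the Sample size section uses the 20 points as the assumed effect, and 500 reproduces with a null of zero. It is a mislabel, not a loss of power.

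**Conclusion.** The concern holds for the power figure. Under the protocol's central assumptions, a test that keeps the two-sided 5% level has power of about 0.75, not 0.85, with 0.84 at ICC 0.01 and 0.67 at ICC 0.03. This assumes an unmatched comparison at 12 months, 35 men analysed in each of ten clusters, 8 degrees of freedom, and no gain from repeated measures or matching. That PASS was run with a normal-theory test is inferred from the exact match to 500; the protocol does not say so.

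The inflated type I error is conditional on a critical value the protocol does not specify, and the margin wording is a labelling error. The point should be fixed. Recruitment is already complete, so what can still be protected is the validity of the final test and the honesty of the stated power.

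**What to change.** 1. In the Analysis section, or in the analysis plan before unblinding, state that the intervention effect is tested with small-sample degrees of freedom, about 8 (between-within, Satterthwaite or Kenward-Roger), with a cluster-level t-test as a check.
2. In the Sample size section, restate power as about 0.75 (0.67 to 0.84 over ICC 0.03 to 0.01). Give the assumptions: unmatched comparison at 12 months, 35 analysed per cluster, no gain from repeated measures or matching.
3. In the Outcomes section, replace the term superiority margin with assumed difference for the sample size, and say that superiority is concluded if the two-sided 95% confidence interval excludes no difference in favour of the intervention.

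The cost is a few sentences and a less favourable power figure. No more men are needed and no trial procedure changes.

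### The 0.85 power for 500 men assumes that the 30% lost men leave the analysis, but one of the protocol's conflicting missing-data rules scores them as non-testers, under which power could be about 0.62

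*Protocol article*

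**What the plan says.** The Sample size section takes testing rates of 70% and 50%, five city clusters in each arm, an ICC of 0.02 from a usual range of 0.01 to 0.03, and a two-sided 5% level. Its target and result are stated as follows: "power = 0.85, and the loss of follow-up is 30%, the total sample size is 500 men (50 for each cluster". PASS 15 is named as the software; no formula is given. The Outcomes section repeats the effect: "An increase of 20% in testing rate (assuming a proportion of HIV testing of 70% in intervention arm and 50% in control arm".

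The Analysis section deals with missing outcomes in three consecutive sentences. Below 15% missing, the analysis is complete case. At 15% or more, missing values are multiply imputed. The third sentence reads: "Participants who miss the follow-up will be included and assumed not achieve the primary and secondary outcomes during the missed follow-up period". No order of precedence is given. The Data collection and management section adds that all survey items are compulsory, so a missing outcome will nearly always mean a missed survey.

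**The concern.** Raising enrolment for expected loss makes up for lost information when the lost men drop out of the analysis. It does not make up for a rule that keeps them in the denominator as failures. Such a rule lowers the observed proportion in both arms and shrinks the difference between them, at any number enrolled. The Sample size section makes no allowance for this.

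The three missing-data sentences also apply to the same men. At the planned 30% loss, a man who misses the 12-month survey cannot be both imputed and scored as a non-tester in one primary analysis. The choice decides whether the trial targets a 20-point difference or a smaller one, and whether the stated power holds. A null result would be read against a claimed power of 0.85.

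**Working it through.** **Inputs.** From the Sample size section: 70% vs 50%, 5 clusters per arm, ICC 0.02 (range 0.01 to 0.03), two-sided alpha 0.05, 30% loss, 50 men enrolled per cluster.

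**Formula (inferred).** Unpooled two-proportion z-test with a design effect:
- DE = 1 + (m − 1) × ICC, where m is the number analysed per cluster
- n_eff = 5m / DE per arm
- SE = √{[p1(1 − p1) + p2(1 − p2)] / n_eff}
- power = Φ(|p1 − p2| / SE − 1.96)

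**Step 1: the plan's own figure.** Lost men removed, m = 50 × 0.7 = 35.
- DE = 1 + 34 × 0.02 = 1.68; n_eff = 175 / 1.68 = 104.2
- SE = √(0.46 / 104.2) = 0.0665; z = 0.20 / 0.0665 = 3.01; power = 0.853
- m = 34 gives 0.847, so 35 is the smallest size that reaches 0.85; 35 / 0.7 = 50 per cluster, or 500 men.

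This matches exactly. Had all 50 been analysed at 70% vs 50%, power would be 0.91, so the step from 35 to 50 serves only to replace men who leave. A pooled-variance version gives 0.843 at m = 35 and a total of 530.

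**Step 2: every lost man scored as a non-tester.** Assume 30% loss in each arm. Then p1 = 0.7 × 70% = 49%, p2 = 0.7 × 50% = 35%, the difference is 14 points, and m = 50.
- ICC 0.02: DE = 1.98; n_eff = 250 / 1.98 = 126.3; SE = √[(0.2499 + 0.2275) / 126.3] = 0.0615; z = 2.28; power = 0.62
- ICC 0.01: DE = 1.49; power = 0.75
- ICC 0.03: DE = 2.47; power = 0.53

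The pooled version at ICC 0.02 gives 0.617.

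**Step 3: an ICC that shrinks with the scoring.** If 0.02 describes the outcome before zero-scoring and retention is the same in every city, the ICC of the scored outcome is 0.7² × 0.02 × p(1 − p) / [0.7p(1 − 0.7p)]. That is 0.0082 for p = 70% and 0.0108 for p = 50%, averaging 0.0095. Power is then about 0.75.

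**Step 4: cumulative uptake, with earlier reported tests counted.** These assumptions are not in the protocol: 7.5% of men are lost at each of the four visits, and testing follows a constant hazard that reaches 70% and 50% at 12 months. A man last seen at visit k (k = 0 to 3) has tested with probability 1 − (1 − p)^(k/4).
- Intervention: 0.7 × 0.70 + 0.075 × (0 + 0.260 + 0.452 + 0.595) = 58.8%
- Control: 0.7 × 0.50 + 0.075 × (0 + 0.159 + 0.293 + 0.405) = 41.4%
- The difference is about 17 points; power is 0.80 at ICC 0.02 (0.90 at 0.01, 0.71 at 0.03).

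**Step 5: lower loss with full non-tester scoring, ICC 0.02.** Power is 0.83 at 10% loss, 0.78 at 15% and 0.73 at 20%. It drops below 0.85 at about 8% loss.

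| Handling of the 30% lost men | Contrast | Power at ICC 0.02 |
|---|---|---|
| Removed, as sized | 70% vs 50% | 0.85 |
| Non-testers, earlier tests count (illustrative) | 58.8% vs 41.4% | 0.80 |
| Non-testers, ICC shrinks | 49% vs 35% | 0.75 |
| Non-testers, ICC stays 0.02 | 49% vs 35% | 0.62 |

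**The case against.** A reader might infer that the analysis does count lost men as non-testers, so that the contrast tested is 49% vs 35% and the true power lies between 0.62 and 0.75. The protocol does not support that as a settled fact, for four reasons.

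- The sentence just before the non-tester rule calls for multiple imputation at 15% or more missing. At 30% loss that would keep the target at 70% vs 50% and power near 0.85, if imputation adds little information. This stands. It makes the low power conditional and exposes a contradiction that must be settled in any case.
- The non-tester rule is limited to the period that was missed. The primary outcome, uptake after 12 months, can be read as any test over the year. A man who reported a test and was lost later would then still count, and Step 4 shows a much milder loss of power. This also stands.
- Only PASS 15 is named, so the formula is inferred. The planned model is a mixed model over four follow-ups, and a single-endpoint z-test does not give its power. This is a fair caution about precision. It does not remove the mismatch, because the sizing itself rests on 70% vs 50% with 35 analysed per cluster.
- Recruitment is complete, so the sample size can no longer be planned afresh. True, but the primary rule and the stated power can still be made consistent.

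On the other side, the non-tester sentence comes last, carries no condition, and is the only one of the three that addresses missed follow-ups. It cannot be set aside as a slip.

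**Conclusion.** The concern holds in conditional form. The sample-size arithmetic is not wrong on its own terms: 500 men and 0.85 reproduce when lost men leave the analysis. What is wrong is that the Analysis section gives incompatible rules for those men, and the stated power does not hold under one of them.

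If non-tester scoring governs, loss is 30% in both arms and every lost man fails on the 12-month endpoint, power is about 0.62 at the protocol's ICC of 0.02, with 0.75 to 0.53 over its range of 0.01 to 0.03. The chance of missing the assumed effect would be about 38%, against the 15% implied. If the ICC shrinks with the scoring, power is about 0.75. If earlier reported tests count, it is about 0.80 under the illustrative assumptions. A flat statement that the trial has 0.62 power would go beyond the document.

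**What to change.** State one primary missing-data rule and make the Sample size, Outcomes and Analysis sections agree with it. There are two consistent choices.

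1. Make the primary analysis one that does not score lost men as failures: multiple imputation at 15% or more missing, as already written. This fits the sizing. Move non-tester scoring to a sensitivity analysis.
2. Keep non-tester scoring as primary and delete the complete-case and imputation rule for missed surveys. Restate the power in the Sample size section (about 0.62, range 0.53 to 0.75 over the stated ICC range, under full zero-scoring) and the expected contrast in the Outcomes section (14 points, 49% vs 35%). If tests reported before dropout are to count, say so and base the restated figures on that definition, with its assumptions.

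No men should be added. The cost is wording. The second choice also means stating a less favourable power.
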